**Figure 1 F1:**
[figure not shown]
**Study design and treatment schema of Enzy-MagIC-study (*****Enzy*****mes,*****Ma*****rathon runnin*****G*****, *****I*****nflammation,*****C*****oagulation-Study).** V1: visit 1 five weeks before marathon race. V2: visit 2 one week before race. V3: visit 3 immediately after race. V4: visit 4 one day after race. V5: visit 5 three days after race. V6: visit 6 two weeks after race. Red dots: study medication. One week before the marathon race, participants will begin daily ingestion of the study medication (3×4 tablets), with intake continued for two weeks after the race (3×2 tablets per day).

A total of 160 healthy male athletes between the ages of 20 and 65 years who intend to participate in the Munich Marathon 2013 will be recruited from August-September 2013. The inclusion and exclusion criteria are presented in Table 1.

**Table 1 T1:** In- and exclusion criteria for participants of the Enzy-MagIC-study

**Inclusion criteria**	**Exclusion criteria**
• Healthy* male	• Known cardiac disease
• Age 20-65 years	• Known allergy against the active ingredient of the study medication or pineapple, papaya, or kiwi
• History of at least one successfully finished half marathon	
• Intention to participate at the Munich Marathon 2013	• Known severe coagulopathy
• Subject is able to read, understand, and sign a written informed consent to participate in the Enzy-MagIC-study	• Known lactose intolerance
	• Pharmaceutical treatment for diabetes mellitus or arterial hypertension
	• Acute or chronic renal failure
	• Acute or chronic liver disease
	• Acute or chronic infection or inflammatory disease
	• Use of medications or supplements influencing immune function
	• Musculoskeletal or psychiatric disease
	• Neoplasia
	• Participation in other interventional trials

*Healthy means in accordance with the current WHO-definition a state of complex physical and mental well-being [41].

The study will be conducted in accordance with Good Clinical Practice guidelines, the guiding principles of the Declaration of Helsinki 2008, and local laws and regulations. The study protocol has been approved by the ethics committee of the University Hospital Klinikum rechts der Isar, Munich, Germany (approval reference number, 5820/13) and the Bundesinstitut für Arzneimittel und Medizinprodukte (BfArM), Bonn, Germany (Vorlagenummer, 4039219).

All participants will have to provide written informed consent. The trial is registered at ClinicalTrials.gov (NCT01916408).

### Interventions

One week before the marathon race, the participants will begin daily ingestion (oral use) of the investigational product Wobenzym (3×4 tablets) and for the two weeks after the marathon race 3×2 tablets. The treatment schema can be seen in Figure 1. Both Wobenzym dosages prior and after the race are in accordance with recommendations in the patient information sheet. In case of heavy inflammatory illnesses or after acute trauma, the dosage can be increased up to 12 tablets per day. Therefore, 12 tablets per day prior to the race should serve as a loading dose before the marathon race representing a inflammatory stimulus. After this loading period, the dosage is decreased to a maintenance dosage of 6 tablets per day. Based on this dosage regime, an adequate plasma concentration of rutoside, trypsin and bromelain can be expected in accordance to the study of Roots et al. [42].

The study product is Wobenzym, an orally applied enzyme-rutoside combination supplement. Each tablet contains 90 mg bromelain, 48 mg trypsin, and 100 mg rutoside. The current indications of the investigational product are swelling and inflammation caused by injuries/trauma, thrombophlebitis and inflammation of joints due to osteoarthritis. Pharmacological investigations in animals have proven no toxic, teratogenic or mutagenic characteristics after single, multiple or long-term intake.

Wobenzym (formerly known as Phlogenzym®) has been on the German market since 1991. Typical adverse reactions of this oral enzyme therapy are a change of consistency, color and odor of the stool. At higher doses, sensations of fullness, flatulence and diarrhea may appear. These symptoms may also be related to the excipient lactose. Very few allergic reactions have been reported. All reported adverse reactions have been minor and disappeared after discontinuation. None of the cases required further treatment. The placebo supplement for the control group consists of lactose-monohydrate and has no active ingredient.

### Laboratory measurements

Blood samples will be collected 5-weeks (visit 1) and 1-week (visit 2) before the race, and immediately (visit 3), 24-h (visit 4), 72-h (visit 5) and 2 weeks (visit 6) after the race. At these visits inflammation measures (IL-6, IL-1-β, IL-10, myeloperoxidase, high-sensitivity C-reactive protein (hs-CRP), leukocyte count) will be analyzed.

Muscle damage parameters (creatine kinase (CK), myoglobin, glutamate oxalacetate (GOT), lactate dehydrogenase (LDH)) will be collected and measured at each visit (1-6). The short form of the McGill-questionnaire will be used to assess muscular strain [43].

Rheological parameters (D-dimer, tissue plasminogen activator (tPA), platelet aggregation) will be collected and measured at each visit (1-6).

### Clinical measurements

Baseline data of the participants will be collected at the first visit. This includes questionnaires assessing training history, history of cardiovascular risk factors, physical examination, anthropometry, clinical chemistry, resting ECG, and echocardiography. One week prior to the race URTI-rates will be assessed daily by the Wisconsin Upper Respiratory Symptom Survey (WURSS-24) and will be compared between treatment and placebo group during the 2-week period following the race. The WURSS-24 is a reliable and valid tool for assessing symptoms, functional impairments, and global severity and global change of common cold [44]. Only complete questionnaires will be used for analyses.

Participants will be requested not to use medications influencing inflammation such as non-steroidal anti-inflammatory drugs. Furthermore, subjects will be asked to refrain from fatty food and from all polyphenol-containing foods, especially beverages such as wine, beer, and fruit juice, as well as fresh and dried fruits or vegetables. Nutritional intake will be recorded with a 3-days nutritional record before visit 2 and before the marathon race.

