#### Secondary endpoints

Secondary endpoints include the effect of consuming Wobenzym on:

1. the frequency of upper respiratory tract infections (URTI) during the 2-week post-marathon period as determined by the Wisconsin Upper Respiratory Symptom Survey (WURSS-24).

2. pre-to-post marathon race changes in salivary IgA concentration.

3. pre-to-post marathon race changes of muscular (e.g. CK, myoglobin, GOT, LDH) and rheological (e.g. D-Dimer, tPA, platelet aggregation) parameters, and muscular strain ( McGill Pain Questionnaire).

4. pre-to-post marathon race changes of cytokine concentrations (e.g. IL-1-β, IL-10), oxidative markers (e.g. myeloperoxidase) and acute-phase-proteins (e.g. high-sensitivity C-reactive protein [hs-CRP]) as well as differential blood and leukocyte count (e.g. leukocytosis).

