### Participants safety

#### Adverse events

Adverse events are undesirable signs or symptoms that occur during the study and may or may not be causally related to the treatment. All adverse events considered at any level to be related to the IMP will be recorded on eCRFs. A common cold or URTI episode is not regarded as an AE in this study.

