### Statistical methods

The difference of logarithmized IL-6 values will be calculated for each participant as distribution of IL-6 differences within the groups is expected to be skewed. Differences of logarithmized values will be compared between both study groups using a two-sample t-test. A two-sided level of significance of 5% will be considered for this primary efficacy analysis. Quantitative secondary endpoints will be analyzed using ANOVA methods, and qualitative data using chi-squared tests. Analysis of the primary endpoint and the secondary efficacy endpoints will be performed following the intention-to-treat (ITT) principle. These endpoints will also be assessed in the per-protocol dataset in the sense of sensitivity analyses.

The ITT dataset will consist of all trial subjects enrolled into the trial and randomized. For subjects with missing post marathon inflammation markers, a conservative replacement of the missing values will be conducted by imputing the lowest observed post marathon value for the placebo group and the highest observed value for the treatment group. The per-protocol dataset includes all trial subjects who were treated according to protocol. A tertiary dataset for analysis is the safety population. This population includes all trial subjects who received any IMP or other trial treatment.

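### The complete-questionnaires-only rule for the WURSS-24 is not reconciled with the intention-to-treat analysis of URTI frequency

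*Protocol article*

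**What the plan says.** Under Clinical measurements, the protocol article has the WURSS-24 filled in daily, starting in the week before the race. URTI rates "will be compared between treatment and placebo group during the 2-week period following the race". The same paragraph closes with the restriction "Only complete questionnaires will be used for analyses".

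Under Secondary endpoints, the first item is "the frequency of upper respiratory tract infections (URTI) during the 2-week post-marathon period", with the WURSS-24 as the means of determining it. No other source for this endpoint is named.

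Under Statistical methods, the article says: "Analysis of the primary endpoint and the secondary efficacy endpoints will be performed following the intention-to-treat (ITT) principle". It defines the population: "The ITT dataset will consist of all trial subjects enrolled into the trial and randomized". Qualitative data are compared by chi-squared tests, and the per-protocol set serves as a sensitivity analysis. The one missing-data rule reads "For subjects with missing post marathon inflammation markers, a conservative replacement of the missing values will be conducted". It does not extend to questionnaire data.

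**The concern.** The article is not silent on incomplete WURSS-24 data. It states a rule, and that rule is complete-case. Read next to an analysis principle that counts everyone randomised, it leaves open how a runner with an incomplete form, or a missing one, enters the URTI comparison. An analyst following the Clinical measurements sentence could report a completers' analysis under an ITT label.

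Two things are at stake. The first is information: observed data are thrown away, and depending on what "complete" means, whole runners may go with them. The second is validity. If runners who feel ill or tolerate the tablets badly fill in the form less reliably, or more reliably, than others, the analysed subset is selected on something related to the outcome, and a chi-squared test on that subset does not correct for it. URTI incidence is part of the trial's stated aim and hypothesis, so this is not a peripheral endpoint.

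**Working it through.** **The plan's own figure.** The only sample size stated is for IL-6: 80 per group, from a CV of 0.60, a 25% relative difference, 90% power and two-sided 0.05. The log-scale SD is √ln(1 + 0.60²) = 0.5545 and the difference is |ln 0.75| = 0.2877. Then n = 2 × (1.960 + 1.282)² × 0.5545² / 0.2877² = 78.1, so 79 per group. The t-test version gives 79.05, rounded up to 80. The stated figure reproduces and is not in dispute. The article gives no URTI rate, power or form-completion rate, so everything below rests on assumed inputs.

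**Reading A: "complete" means the whole post-race diary.** The comparison window is 14 days. Let p be the assumed chance that a runner misses a given day.

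- Independent gaps: share with at least one gap = 1 − (1 − p)^14.
- Gaps clustered within runners: a beta-binomial with mean p and assumed within-runner correlation 0.2. With a + b = 1/0.2 − 1 = 4 and b = 4(1 − p), the share with at least one gap = 1 − ∏ (b + i)/(4 + i), for i = 0 to 13.

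| Assumed p | Lost, independent | Left of 80 | Lost, clustered | Left of 80 |
|---|---|---|---|---|
| 1% | 13% | 69 | 6% | 75 |
| 2% | 25% | 60 | 12% | 70 |
| 3% | 35% | 52 | 18% | 66 |
| 5% | 51% | 39 | 28% | 58 |

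For example, at 3% the independent case gives 1 − 0.97^14 = 0.347.

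**What the loss could cost in power.** Assume URTI rates of 40% and 20%. With the usual two-proportion normal approximation (pooled variance under the null), power is 79% at 80 per group, 67% at 60 and 49% at 39.

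**Reading B: "complete" means each daily form.** Runners with any usable form stay in, and partly completed days are removed. Whether an episode disappears depends on how many days it spans and on the case definition, so no figure can be derived.

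**Possible bias, either arm.** The observed rate among completers is π·c₁ / (π·c₁ + (1 − π)·c₀), where π is the true rate and c₁, c₀ are the completion rates among ill and well runners. Assume π = 30% in both arms and c₀ = 90%.

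- c₁ = 90% in one arm: observed 30%.
- c₁ = 60% in the other: 0.18 / (0.18 + 0.63) = 22%.

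That is a spurious difference of 8 percentage points with no true effect. If c₁ = 60% in both arms, both read 22% and no difference is created.

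**The case against.** The strongest reply is that the two rules need not collide. The instrument is filled in daily, so a questionnaire can naturally be read as one day's form. On that reading a runner with a partly filled day stays in the ITT comparison. This stands. A reader might infer that the two sections cannot both hold, or that a single skipped item or day removes a runner, but the text does not settle which unit is meant.

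The sizes are also open to challenge. The missed-day rates are assumed, and diary gaps tend to concentrate in a few people. That stands too, which is why the clustered column is shown; it roughly halves the loss. Extending the count to 21 days would inflate it further, but the week before the race lies outside the comparison window.

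On the per-form reading, one might infer that URTI is bound to be under-counted. It is not: an episode spanning several days can survive the loss of one form.

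A reader might also point to the Adverse events section, "A common cold or URTI episode is not regarded as an AE in this study", and conclude that an episode on a discarded form is counted nowhere. That goes too far. Routine recording there covers only events judged related to the product, so an unrelated cold would go unrecorded anyway, while serious events are recorded whatever the cause. Adverse-event recording is not the source for this endpoint.

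Finally, nothing in the article shows that completeness depends on illness or on arm, and the trial is double-blind. The bias is a possibility only.

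What the reply does not remove is the stated rule. On either reading it discards observed data, and nothing links it to the ITT analysis.

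**Conclusion.** The point holds as a stated complete-case rule that is not reconciled with the ITT principle for the same endpoint. It is a defect in what the article says, not a detail left to an analysis plan. That conclusion rests on the text alone.

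Its size is illustrative. On the whole-diary reading the loss is about 13% to 51% of runners with independent gaps and about 6% to 28% with clustered gaps, for assumed missed-day rates of 1% to 5%. On the per-form reading the loss is of days, and a missed episode is possible but not certain. Bias in the chi-squared comparison requires completeness to be related to illness or tolerability, which is plausible but undocumented. It touches the URTI endpoint, not the primary IL-6 analysis or its sample size, so the change should be made but does not threaten the main conclusion.

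**What to change.** Replace the complete-only sentence under Clinical measurements with a rule stating that:

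- the main URTI analysis uses every daily form received, including partly completed ones;
- all randomised runners are kept in that analysis;
- a URTI case rule says how a runner is classified from a partial form or a partial diary;
- a missing-data method, for example multiple imputation, covers runners whose URTI status stays undetermined;
- the complete-questionnaire analysis is kept as a sensitivity analysis, with "complete" defined.

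The case rule and the missing-data method must be fixed before unblinding. The cost is a wording change and modest extra programming. The small downside is that a rule for partial forms has to be chosen in advance; the article offers no basis for any particular item threshold, so the choice should be justified where it is made.

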### Endpoints

#### Primary endpoint

The primary endpoint criterion is the effect of Wobenzym compared to placebo on plasma IL-6 concentration changes following the marathon race.

#### Secondary endpoints

Secondary endpoints include the effect of consuming Wobenzym on:

1. the frequency of upper respiratory tract infections (URTI) during the 2-week post-marathon period as determined by the Wisconsin Upper Respiratory Symptom Survey (WURSS-24).

2. pre-to-post marathon race changes in salivary IgA concentration.

3. pre-to-post marathon race changes of muscular (e.g. CK, myoglobin, GOT, LDH) and rheological (e.g. D-Dimer, tPA, platelet aggregation) parameters, and muscular strain ( McGill Pain Questionnaire).

4. pre-to-post marathon race changes of cytokine concentrations (e.g. IL-1-β, IL-10), oxidative markers (e.g. myeloperoxidase) and acute-phase-proteins (e.g. high-sensitivity C-reactive protein [hs-CRP]) as well as differential blood and leukocyte count (e.g. leukocytosis).

### Sample size

Sample size calculation was based on the primary endpoint criterion, the difference in marathon-induced change of plasma IL-6 between the study groups. Due to the expected right-skewed distribution of IL-6, differences in changes of logarithmized IL-6 levels (relative group changes) were considered as the base for inferential statistics. From previous publications a coefficient of variation (CV) of 0.60 for IL-6 changes was expected for the proposed study population [45]. Assuming a true relative difference of at least 25% between the groups, a sample size of 80 individuals per group is necessary to detect a difference in IL-6 changes between both groups (given the CV of 0.60) with a power of 90% on a two-sided level of significance of 0.05.

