#### Discontinuation

Participants have the right to withdraw from the clinical trial at any time and in any case without giving a reason. The investigator has the right to withdraw a subject for any reason which is in the best interests of the subject, including intercurrent illness or adverse events. Discontinued participants will not be replaced.

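### The 80 per group gives 90% power only if no runner is lost; exactly 80 per group are randomised, nobody is replaced, and the power statement makes no allowance for loss

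*Protocol article*

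**What the plan says.** All references are to the protocol article.

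- **Sample size.** The effect is stated as "Assuming a true relative difference of at least 25% between the groups", the variability as "a coefficient of variation (CV) of 0.60 for IL-6 changes was expected for the proposed study population". The working scale is logarithmic: "differences in changes of logarithmized IL-6 levels (relative group changes) were considered as the base for inferential statistics". The result is that "a sample size of 80 individuals per group is necessary to detect a difference in IL-6 changes between both groups", "with a power of 90% on a two-sided level of significance of 0.05". No loss rate and no inflation for loss appear.
- **Number randomised.** The Abstract randomises 160 men, and Randomization sets a 1:1 ratio, so 80 per group. Design and participants gives the same total: "A total of 160 healthy male athletes between the ages of 20 and 65 years who intend to participate in the Munich Marathon 2013".
- **Discontinuation.** Men may withdraw at any time, the investigator may withdraw them, and "Discontinued participants will not be replaced".
- **Statistical methods.** For the primary endpoint, "Differences of logarithmized values will be compared between both study groups using a two-sample t-test". The intention-to-treat set is everyone randomised. Missing post-race markers are filled with the smallest value seen after the race under placebo and the largest seen under active treatment.

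**The concern.** The number needed and the number randomised are the same, while the document expects some men to withdraw or to lack a post-race sample and rules out replacing them. Entry requires the intention to run and one finished half marathon, but neither guarantees a post-race IL-6 value. If 80 is the requirement with every value observed, any loss takes the trial below its stated power.

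What is at stake is how a null primary result is read. A reader told that the trial had 90% power for a 25% reduction will take a null result as fairly strong evidence against such an effect. That inference is weaker if runners were lost, and much weaker if their values were imputed against the treatment.

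**Working it through.** **Inputs.** Two-sided level 0.05, power 90%, relative difference 25% and CV 0.60 come from Sample size. The t-test on log differences comes from Statistical methods. Loss rates and the between-runner SD of baseline log IL-6 are not in the document and are assumed below.

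**1. Reproducing the 80.**
- Log-scale SD from the CV (log-normal): sqrt(ln(1 + 0.60²)) = sqrt(ln 1.36) = 0.5545.
- Effect for a 25% reduction: |ln 0.75| = 0.2877.
- Standardised effect: 0.2877 / 0.5545 = 0.519.
- Normal approximation: n = 2 × (1.960 + 1.282)² × 0.5545² / 0.2877² = 78.1, so 79 per group.
- Exact t-test: n = 79.05, so 80 per group.
- Exact t-test power: 90.3% at 80 and 89.98% at 79.

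The plan's figure is confirmed. It is the smallest whole number that reaches 90%, so it holds no reserve.

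**2. Power if runners without both values are left out** (exact t-test, equal loss in both groups):

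| Assumed loss | Left per group | Power |
|---|---|---|
| 0% | 80 | 90.3% |
| 5% | 76 | 88.8% |
| 10% | 72 | 87.1% |
| 15% | 68 | 85.2% |
| 20% | 64 | 83.0% |

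**3. Power under the imputation rule.** Simulation with 80 per group, true ratio 0.75, SD of the log change 0.5545, equal numbers missing at random in both groups, baseline observed, and the extreme value taken within each arm. The baseline log SD is assumed to lie between 0.5 (lower figure) and 0 (higher figure). Power means a significant result in favour of treatment.

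| Missing per group | Simulated power |
|---|---|
| 1 | about 74–80% |
| 2 | about 51–67% |
| 4 (5%) | about 14–34% |
| 8 (10%) | under 5% |

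Repeated runs moved these limits by a point or two.

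The size can be checked by hand for a baseline SD of 0. The largest of about 79 standard normal values is expected near 2.4, so an imputed value lies about 2.4 × 0.5545 = 1.33 from its arm's mean, in the unfavourable direction. One such value per arm shrinks the contrast by 2 × 1.33 / 80 = 0.033, from 0.288 to about 0.254. Four per arm shrink it by 0.133, to about 0.155, roughly half the planned effect. The imputed extremes also raise the within-group SD, which lowers power further.

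**The case against.** **The figure is right as stated.** Under its inputs, 80 individuals per group does give 90% power. This stands: there is no arithmetic error, and the point is the missing condition.

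**The attrition effect is small.** A 5% loss costs about 1.5 points and 10% about 3 points, within the uncertainty of an assumed CV and an assumed effect. This also stands for an analysis of observed values.

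**Intention to treat keeps all 80 per group.** Nominally it does, so the complete-case table does not describe the planned primary analysis. This does not rescue the 90%, because the rule that keeps the numbers whole shifts the contrast against treatment and widens the spread. The merits of that rule are a separate matter; here it counts only because the stated power does not reflect it.

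**An article may leave attrition to the full protocol.** It may, but this article gives both the number needed and the number randomised, and they are equal.

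Some stronger readings are tempting but unsupported:

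- *The trial needs 131 per group.* That follows from a ratio of 1.25 or 0.80. The Discussion hypothesises a lower IL-6 on treatment, and 0.75 is the reading that reproduces 80.
- *The five weeks between the first visit and the race erode the 80.* The timing of randomisation is in Figure 1, which is not available here. Losses before randomisation would not reduce the 80.
- *Baseline adjustment would make up the shortfall.* That depends on the pre/post correlation of log IL-6, which the document does not give.

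**Conclusion.** The point holds as a missing condition on the power statement. The 90% applies to 80 runners per group with both IL-6 values observed. The trial randomises exactly that number, foresees losses and does not replace them.

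The size depends on a loss rate that the document does not give, so it would be wrong to infer that the trial is underpowered by a known amount. Leaving out lost runners costs 1.5 to 7 points from the 90.3% over assumed losses of 5 to 20%. Under the planned imputation the cost is severe: one missing value per group already takes power to about 74–80%. Those figures rest on equal missingness, within-arm extremes and an assumed baseline log SD of 0 to 0.5. If the extremes were taken over both arms together, power would be lower still (about 4–17% with four missing per group). Under either reading, the power in Sample size and the primary analysis in Statistical methods do not match.

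**What to change.** Restate the conclusion of Sample size along these lines:

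> Eighty runners per group with observed pre- and post-race IL-6 give 90% power for a geometric mean ratio of 0.75 (active to placebo). With 10–20% of runners lost, complete-case power is 87–83%.

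Then add the power under the missing-data method actually used for the primary analysis, with the assumed loss rate and its basis. Writing the 25% as a ratio of 0.75 also removes any doubt about its direction.

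For scale, keeping 80 observed runners per group would have meant randomising 80 / (1 − loss): 85, 89, 95 or 100 per group at 5, 10, 15 or 20% loss. This restores 90% only for an analysis of observed values, not under the present imputation.

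The rewording takes a sentence or two and needs no change to the conduct of the trial. Its downside is that the stated power becomes less favourable.
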